# Whole brain radiotherapy versus stereotactic radiosurgery for 4–10 brain metastases: a phase III randomised multicentre trial

**DOI:** 10.1186/s12885-017-3494-z

**Published:** 2017-07-25

**Keywords:** Brain metastases, Stereotactic radiosurgery, Whole brain radiotherapy, Quality of life

## Abstract

**Background:**

Maintenance of quality of life is the primary goal during treatment of brain metastases (BM). This is a protocol of an ongoing phase III randomised multicentre study. This study aims to determine the exact additional palliative value of stereotactic radiosurgery (SRS) over whole brain radiotherapy (WBRT) in patients with 4–10 BM.

**Methods:**

The study will include patients with 4–10 BM from solid primary tumours diagnosed on a high-resolution contrast-enhanced MRI scan with a maximum lesional diameter of 2.5 cm in any direction and a maximum cumulative lesional volume of 30 cm^3^. Patients will be randomised between WBRT in five fractions of 4 Gy to a total dose of 20 Gy (standard arm) and single dose SRS to the BMs (study arm) in the range of 15–24 Gy. The largest BM or a localisation in the brainstem will determine the prescribed SRS dose. The primary endpoint is difference in quality of life (EQ5D EUROQOL score) at 3 months after radiotherapy with regard to baseline. Secondary endpoints are difference in quality of life (EQ5D EUROQOL questionnaire) at 6, 9 and 12 months after radiotherapy with regard to baseline. Other secondary endpoints are at 3, 6, 9 and 12 months after radiotherapy survival, Karnofsky ≥ 70, WHO performance status, steroid use (mg), toxicity according to CTCAE V4.0 including hair loss, fatigue, brain salvage during follow-up, type of salvage, time to salvage after randomisation and Barthel index. Facultative secondary endpoints are neurocognition with the Hopkins verbal learning test revised, quality of life EORTC QLQ-C30, quality of life EORTC BN20 brain module and fatigue scale EORTC QLQ-FA13.

**Discussion:**

Worldwide, most patients with more than 4 BM will be treated with WBRT. Considering the potential advantages of SRS over WBRT, i.e. limiting radiation doses to uninvolved brain and a high rate of local tumour control by just a single treatment with fewer side effects, such as hair loss and fatigue, compared to WBRT, SRS might be a suitable alternative for patients with 4–10 BM.

**Trial registration:**

Trial registration number: NCT02353000, trial registration date 15^th^ January 2015, open for accrual 1^st^ July 2016, nine patients were enrolled in this trial on 14^th^ April 2017.

## Background

In this randomised study, in patients with 4–10 brain metastases (BM), the standard treatment of whole brain radiotherapy (WBRT) is compared to stereotactic radiosurgery (SRS) for all lesions with the primary endpoint of quality of life (QOL) at 3 months after radiotherapy. We hypothesise that SRS provides better QOL than WBRT because of better local tumour control and avoidance of potential side effects of WBRT. Brain metastases are an important cause of morbidity and mortality in patients with metastasised cancer, and therefore, optimal tumour control is essential. Dutch guideline recommends SRS for patients with 1–3 BM and WBRT for patients with 4 or more BM. WBRT has side effects such as hair loss, fatigue and cognitive dysfunction, which may result in decreased QOL that is undesirable in a palliative setting. [1] There are important advantages of SRS over WBRT, i.e., limiting radiation doses to the uninvolved brain and a high rate of local tumour control by just a single treatment compared to WBRT, in which a relatively low palliative radiation dose is delivered to both the brain and the BM (Fig. 1). SRS is widely available in most Dutch radiotherapy centers. Because of recent technical advances, SRS can be delivered in relatively short treatment time in 10–45 min in patients with multiple BM. With SRS, there is a relatively low risk (±5%) of symptomatic radionecrosis: damage of the surrounding brain tissue, which may occur several months after treatment. Radionecrosis may cause neurologic symptoms, often temporary, which are treated with dexamethasone. Moreover, the clinical value of WBRT over the best supportive care is controversial. A recent interim analysis of the QUARTZ study showed equal QOL and survival for patients treated with WBRT versus treatment with steroids alone. [2] A recent (non-randomised) study in a large cohort of patients with BM showed that after SRS, survival of patients with 5–10 BM was comparable to that of patients treated with 2–4 BM. [3] Thus far, WBRT has never been compared directly with SRS in patients with 4–10 BM, and therefore a randomised trial is needed. In the United States, the NAGKC 12–01 (NCT01731704) was initiated in patients with 5 or more brain metastases in which SRS was directly compared with WBRT. However, this study was closed prior to enrolment of patients because of insufficient staff. Many systemic therapies do not have satisfactory tumour control of BM because of poor passage of the blood brain barrier. In the future, SRS may be the optimal treatment choice to control BM in patients with multiple brain metastases to maintain long-term QOL, whereas new innovative systemic therapies may control extracranial disease.

**Fig. 1 Fig1:**
[figure not shown]
Dose distribution difference between WBRT (*left*) and SRS (*right*). A typical dose distribution on a planning-CT of WBRT on the left side and SRS on the right side. With WBRT, the healthy brain tissue receives the same low palliative radiation dose (non-ablative). With SRS, only the metastatic tissue receives a high ablative dose

## Methods/design

### Design

The study is a randomised phase III study with two study arms. The standard arm is WBRT and the experimental arm is SRS. We hypothesise that SRS provides better QOL than WBRT because of better local tumour control and avoidance of potential side effects of WBRT.

### Objectives and endpoints

The primary objective is to determine whether QOL is better preserved after SRS than after WBRT in patients with 4–10 BM. The primary endpoint is difference in QOL (EQ5D EUROQOL score) at 3 months after radiotherapy with regard to baseline. The secondary objective is to determine whether SRS provides better survival and less toxicity than WBRT. [1, 2] Secondary endpoints are difference in QOL (EQ5D EUROQOL questionnaire) at 6, 9 and 12 months after radiotherapy with regard to baseline, survival at 3, 6, 9 and 12 months after radiotherapy, Karnofsky ≥ 70, WHO performance status, steroid use (mg), toxicity according CTCAE V4.0 including hair loss, fatigue, neurocognition and brain salvage during follow-up, type of salvage, time to salvage after randomisation and Barthel index. Facultative secondary endpoints are neurocognition with the Hopkins verbal learning test, quality of life EORTC QLQ-C30, quality of life EORTC BN20 brain module and fatigue scale EORTC QLQ-FA13.

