### Study population

The study will include patients with 4–10 BM from solid tumours diagnosed on a high resolution contrast-enhanced MRI scan referred for radiotherapy, with a maximum lesional diameter of 2.5 cm. Before randomisation, a new neuronavigation MRI (T1 gadolinium) is made for the definitive evaluation of the inclusion and exclusion criteria. The inclusion criteria are age ≥ 18; minimum of 4 BM up to a maximum of 10 BM on diagnostic MRI scan; maximum diameter of single gross tumour volume (GTV) 2.5 cm; maximum cumulative GTV of 30 cm^3^; Karnofsky performance status ≥70; any solid primary tumour, and patients’ ability to provide written informed consent. Small cell lung carcinoma, germinoma and lymphoma are excluded. Other exclusion criteria are a contraindication for MRI, prior treatment for BM (i.e. surgery, SRS or WBRT), concurrent use of systemic therapy (systemic therapies should be stopped at least 1 week prior until 1 week after the radiotherapy), maximum cumulative GTV of more than 30 cm^3^ on planning-MRI, more than 10 BM on planning-MRI, leptomeningeal disease and brainstem metastasis with a PTV of more than 20 cm^3^. If a patient is not eligible based on the inclusion or exclusion criteria of this study based on the planning-MRI results prior to randomisation (e.g. >10 BM, GTV diameter > 2.5 cm, cumulative GTV > 30 cm^3^), these non-eligible patients will be replaced by a new patient. These patients are not included in the statistical analysis of the trial.

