Patients will be immobilised in a supine position within a thermoplastic mask or stereotactic noninvasive frame, with or without bite block and/or other fixation, according to institutional standards for SRS. The accuracy of the stereotactic fixation system should be good enough to justify the CTV to PTV margin used. This means the intrafraction motion should at least be within the CTV-PTV margin used. If a margin of 0 mm is used, the maximum intrafraction motion should be <0.5 mm, with the SD being less than 0.25 mm. A planning CT scan with ≤2 mm thick contiguous slices (preferable CT slice thickness = 1 mm) will be fused to a contrast-enhanced stereotactic MRI scan. The interval between the planning-MRI and actual SRS treatment is a maximum of 3 weeks. Single or multiple isocentres are allowed for delivering SRS according to the preference of treatment center. Tissue density inhomogeneity correction will be used. Positional verification and correction prior to (and/or during) radiation should be executed according to the institutional protocol for stereotactic radiotherapy and should be in accordance with the CTV-PTV margin used. All techniques that result in the dose requirements being met are allowed. Participating institutes will have to define their radiation delivery treatment prior to the initiation of the study. Techniques that have a shorter treatment time duration are preferred as this is more comfortable for the patient and might prevent an increase in the intrafraction displacement over the treatment time. All vendors are allowed to deliver SRS, such as a linear accelerator, Gamma Knife and CyberKnife.

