### Number of patients and recruitment

Questionnaires measuring QOL with the EQ5D EUROQOL questionnaire are collected from patients with multiple BM treated with WBRT or SRS at baseline and at 3 months after treatment. For this phase III trial, sample size calculation is based on the clinically relevant difference of 0.10 points of the EQ5D-5 L index value (range 0–1) at 3 months after treatment with regard to baseline, with a standard deviation of 0.25 points. For every patient this difference in EQ5D-5 L QOL score is calculated (score at 3 months minus score at baseline). The average score of all patients in the SRS group is calculated and this average score is compared to the calculated average score of all patients in the WBRT group. This is accordingly the method described by Pickard. [6] Sample size calculation is performed for a comparison of means with two-sided alpha 0.05 and power of 0.80. This leads to a sample size per group of 100 patients. To account for drop out, the sample size for this study will be increased by 15% to 230 patients (115 per group). After 86 patients treated, an interim analysis is performed to monitor the safety of the trial regarding the experimental SRS arm.

Patient accrual was started on 1^st^ July, 2016. Up to 14^th^ April, 2017, nine patients were randomised. With expected participation of 12 centres, it is estimated that patient’s accrual can be completed within 2 years with an expected accrual of 10–15 patients each year per centre.

For this phase III study, a comparison of the above described difference in EQ5D score between SRS and WBRT group will be performed using an independent samples Student’s t-test with two-sided significance level alpha set at 0.05. A clinical significant difference in EQ5D is determined at 0.10 points in the index score. [4] For the total patient cohort, a multivariate analysis is performed to identify prognostic factors for a difference in EQ5D score at 3 months with regard to baseline. Differences in secondary endpoints that repeat in time are analysed with Kaplan Meyer curves including log-rank test or ANOVA test. Time-to-event data (e.g. overall survival) will be compared using Kaplan–Meier curves and log-rank test. Means will be compared using independent samples Student’s t-tests. Frequencies (e.g. WHO-PFS) will be compared using Chi-square test.

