## Discussion

A typical SRS treatment requires a high-resolution contrast-enhanced planning-MRI, frameless mask, a planning-CT, a treatment plan and quality assurance. Generally, all preparations will take a maximum of 2 weeks. Duration of SRS delivery depends on the number of isocentres, arcs and dose rate, but usually in the range of several minutes up to 45 min. With WBRT, all other preparation steps are required, but treatment planning and quality assurance are less complex. WBRT treatment is delivered in five fractions compared to a single treatment fraction with SRS. Questionnaires will be assessed at baseline, 3 months after treatment and every 3 months thereafter until 1 year after treatment. Questionnaires can be assessed by telephone, or during scheduled outpatient clinic visits. Not all hospitals have the logistic capacity to perform neurocognitive tests and extensive QOL assessment; hence, neurocognition (Hopkins Verbal Learning Test) and more extensive QOL (EORTC QLQ-C30, EORTC BN20, and EORTC QLQ-FA13) will be facultative endpoints and will only be performed at baseline and at 3 months after radiotherapy at the outpatient clinic in centres willing to participate. Although these secondary endpoints are facultative, these endpoints will also provide valuable information, and participating centres are recommended to monitor them.

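### Survival is counted from radiotherapy while salvage is counted from randomisation, so a randomised patient who is never irradiated has no survival time zero

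*Protocol article*

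**What the plan says.** All references are to the protocol article.

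- **Survival.** Objectives and endpoints lists "survival at 3, 6, 9 and 12 months after radiotherapy". The abstract uses the same origin.
- **Salvage.** The same sentence of Objectives and endpoints has "time to salvage after randomisation".
- **Primary endpoint.** "The primary endpoint is difference in QOL (EQ5D EUROQOL score) at 3 months after radiotherapy with regard to baseline".
- **Analysis.** Number of patients and recruitment states: "Time-to-event data (e.g. overall survival) will be compared using Kaplan–Meier curves and log-rank test". It names no origin.
- **Events around randomisation.** Study population: "Before randomisation, a new neuronavigation MRI (T1 gadolinium) is made for the definitive evaluation of the inclusion and exclusion criteria". Study procedures of SRS: "The interval between the planning-MRI and actual SRS treatment is a maximum of 3 weeks". No corresponding limit is given for WBRT.
- **Course length.** Discussion: "WBRT treatment is delivered in five fractions compared to a single treatment fraction with SRS". Study procedures WBRT spreads the five fractions over five working days in a row. The Discussion adds that preparation generally takes two weeks at most, and that WBRT needs the other steps too but has simpler planning and quality assurance.

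The article does not say whether the radiotherapy origin is the first or the last fraction, or how a randomised but untreated patient is timed.

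**The concern.** The secondary objective asks whether SRS gives better survival than WBRT. That is a comparison between randomised groups, and it is protected by randomisation only if follow-up starts at randomisation for everyone. Starting it at radiotherapy has two consequences.

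First, a patient who is randomised and then dies, withdraws or becomes too ill before treatment has no start date for survival. An analyst who follows the definition literally must either drop the patient or invent a date. Dropping such patients is selection after randomisation, and they are probably the ones with the worst prognosis.

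Second, the start can depend on the arm. If the clock starts when treatment is complete, WBRT starts it several days after its first fraction, and SRS on the day of its only fraction. Different planning complexity may also change the wait before treatment.

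The survival and salvage results would also be reported on two different time axes for the same patients.

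**Working it through.** **1. The plan's own figure.** The article's only quantity nearby is the sample size. With a difference of 0.10, SD 0.25, two-sided alpha 0.05 and power 0.80:

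n per arm = 2 × (1.960 + 0.842)² × 0.25² / 0.10² = 98.1, so 99. The t-test version gives 99.1, rounded up to the stated 100. Then 100 × 1.15 = 115 per arm.

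This figure does not depend on the time origin of survival, so the fix leaves it unchanged.

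**2. The origins side by side.**

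| Endpoint | Origin stated |
|---|---|
| EQ5D change at 3 months (primary) | radiotherapy |
| Survival at the four fixed times | radiotherapy |
| Time to salvage | randomisation |
| Overall survival, Kaplan–Meier and log-rank | none |

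The analysis text does not override the radiotherapy origin in the endpoint definition.

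**3. How long the wait could be.** The article gives no interval from randomisation to treatment. The 3-week limit runs from the planning MRI to SRS, and that MRI is made before randomisation. The wait from randomisation to SRS is therefore 3 weeks minus the time from MRI to randomisation, at most. The two-week preparation time also includes the planning MRI. I assume 7, 14 and 21 days, with 21 as an extreme.

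**4. Deaths before time zero.** The article gives no survival rates. Assume a constant hazard and median survival m of 6 or 9 months (30.44 days per month):

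P(death within d days) = 1 − exp(−ln 2 × d / (30.44 m)), multiplied by 115 for the expected number per arm.

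| Wait | m = 6 months | m = 9 months |
|---|---|---|
| 7 days | 2.6% (3.0) | 1.8% (2.0) |
| 14 days | 5.2% (6.0) | 3.5% (4.0) |
| 21 days | 7.7% (8.8) | 5.2% (6.0) |

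The range is about 2% to 8%, or 2 to 9 of 115 per arm. The result is sensitive to the assumed median: at m = 3 months it would be 5.2% (6.0) at 7 days and 14.7% (16.9) at 21 days.

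**5. Different clock starts.** Five consecutive working days put the last WBRT fraction 4 days after the first, or 6 days if a weekend falls between. Suppose all randomised patients stay in the denominator, true survival is identical, and one arm's clock starts d days later. The 3-month point (91.3 days) then shifts by S(91.3) − S(91.3 + d):

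| Offset | m = 6 months | m = 9 months |
|---|---|---|
| 4 days | 1.1 points | 0.8 points |
| 7 days | 1.9 points | 1.4 points |
| 14 days | 3.7 points | 2.8 points |

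If untreated patients are dropped instead, a constant hazard shared by all patients produces no spurious difference between arms, because those left have the same hazard whenever their clock starts. Bias then comes from who is dropped: frail patients lost at different rates by arm. The article has no data from which to estimate that.

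**The case against.** The strongest reply is that nothing in the article removes untreated patients. The only stated exclusion from analysis concerns patients found ineligible before randomisation. The abstract puts the radiotherapy-based time points in front of a whole run of secondary endpoints, which can be read as a visit schedule, and a condensed article may leave the Kaplan–Meier origin to the full protocol. The first part stands: a reader might infer that the plan excludes deaths before treatment, and no sentence says so. The rest does not remove the point. Objectives and endpoints attaches the radiotherapy origin directly to survival and gives salvage a different one. This is a stated definition, not an omitted detail.

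Other parts of the reply also stand:

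- The 3-week limit cannot be taken as the wait after randomisation, because the MRI comes first. Patients screened with a Karnofsky score of at least 70 may also have a lower early hazard than a constant-hazard model assumes.
- No direction follows. Simpler WBRT planning may start that clock earlier, while the five-day course may start it later.
- A reader might call this immortal time bias. That label does not fit, because a clock that starts at treatment in both arms credits neither with guaranteed survival. The risk is post-randomisation selection.
- A reader might extend the point to the primary endpoint. Timing questionnaires from treatment keeps time since exposure equal, which suits a hypothesis about side effects. A patient who dies before 3 months has no EQ5D score on either clock, and one who declines but is still irradiated does have a time zero. For the same reason, early deaths should not be set against the drop-out allowance of 15 per arm as if moving the origin would recover them.

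**Conclusion.** The concern holds for survival and for the inconsistent time origins. As worded, survival starts at an event after randomisation, a never-irradiated patient has no start date, and the start can differ by arm. The comparison in the secondary objective is therefore not fully protected by randomisation.

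Under the stated assumptions (constant hazard, median 6 to 9 months, wait of 1 to 3 weeks), 2 to 9 of 115 patients per arm would die before time zero, and the upper end is unlikely. A difference in clock start of up to a week would move 3-month survival by less than 2 percentage points. Actual size and direction cannot be derived from the article. The documents do not support the stronger readings: that untreated patients are excluded by plan, or that the primary quality-of-life comparison is invalid.

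**What to change.** State that overall survival, including survival at the four fixed time points, and every other time-to-event endpoint are counted from the date of randomisation for all randomised patients, whether or not radiotherapy was given. Salvage already follows this rule. Quality-of-life visits may stay tied to radiotherapy. Record the time from randomisation to each assessment so that any difference between arms can be seen.

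The cost is a change of wording. Time to salvage already requires the randomisation date, the sample size is unaffected, and the article reports only nine patients randomised by 14 April 2017. Because visits are not rescheduled, no patient is put on a second schedule. The small downside is that the survival time points will no longer coincide exactly with the post-treatment visits.

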### Study population

The study will include patients with 4–10 BM from solid tumours diagnosed on a high resolution contrast-enhanced MRI scan referred for radiotherapy, with a maximum lesional diameter of 2.5 cm. Before randomisation, a new neuronavigation MRI (T1 gadolinium) is made for the definitive evaluation of the inclusion and exclusion criteria. The inclusion criteria are age ≥ 18; minimum of 4 BM up to a maximum of 10 BM on diagnostic MRI scan; maximum diameter of single gross tumour volume (GTV) 2.5 cm; maximum cumulative GTV of 30 cm^3^; Karnofsky performance status ≥70; any solid primary tumour, and patients’ ability to provide written informed consent. Small cell lung carcinoma, germinoma and lymphoma are excluded. Other exclusion criteria are a contraindication for MRI, prior treatment for BM (i.e. surgery, SRS or WBRT), concurrent use of systemic therapy (systemic therapies should be stopped at least 1 week prior until 1 week after the radiotherapy), maximum cumulative GTV of more than 30 cm^3^ on planning-MRI, more than 10 BM on planning-MRI, leptomeningeal disease and brainstem metastasis with a PTV of more than 20 cm^3^. If a patient is not eligible based on the inclusion or exclusion criteria of this study based on the planning-MRI results prior to randomisation (e.g. >10 BM, GTV diameter > 2.5 cm, cumulative GTV > 30 cm^3^), these non-eligible patients will be replaced by a new patient. These patients are not included in the statistical analysis of the trial.

